**Child Behavior Checklist (CBCL)**

The parent/caregiver of the child completed the Child Behaviour Checklist (CBCL). The Child Behaviour Checklist has been used to determine the extent of behavioural anomalies amongst children and adolescents. It contains 113 items, which were rated on a three- point Likert scale, of which items corresponding to ADHD symptoms will be considered. According to the normative data of the CBCL, a t-score ≤ 59 indicates non-clinical symptoms, a t-score between 60 and 64 indicates that the child is at risk for problem behaviours, and a t-score ≥ 65 indicates clinical symptoms

**Outcomes**

Primary outcomes: Primary networks (sensory, visual, and limbic)

Secondary outcomes: Higher-order networks (salience network, dorsal attention network, default mode network, fronto-parietal network)

Brain hubs corresponding to the mentioned networks will be studied

Cortical thickness from DK atlas and subcortical volumes will be used.

**Exposure**

Moderately preterm (32 - 34 weeks)

Very preterm (< 32 weeks)

Full-term (39 – 40 weeks)

**Covariates**

Age at time of MR scan, Sex, Socio-economic status (maternal education, household income, and neighbor area index), and scanner sites. These variables were selected as they known to be associated with cognitive outcomes or brain development.

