**Hypotheses**

Children born before 34 weeks with cognitive deficits will show mixed patterns of cortical thickness (i.e., thinner in primary sensory hubs and thicker in higher-order cognitive hubs) and smaller subcortical volumes at 10 years of age compared to both children born before 34 weeks without cognitive deficits and those born at term without cognitive deficits.

We expect higher structural covariance (stronger connection/coordination) in primary sensory networks and lower structural covariance (weaker connection/coordination) in higher-order networks in children born before 34 weeks with cognitive deficits.

We will extract individual structural covariance values only for the networks that show significant differences in the primary analysis and explore their relationship with behavioral outcomes, such as ASD and ADHD symptoms at 12 years of age.

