**Analysis**

Linear regression model will be used to investigate whether brain structures (cortical thickness and subcortical volumes) differ between children with and without cognitive deficits (presented as standardized beta and 95% CI)

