**Secondary analysis:**

- Very preterm with cognitive deficits Vs. full-term without cognitive deficits
- Moderately preterm with cognitive deficits Vs. full-term without cognitive deficits

All models will be adjusted for above-mentioned confounders/covariates.

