**Constructing of Structural Covariance Networks (SCN):**

To investigate SCN, Pearson partial correlation analysis will be conducted on the brain hubs. This analysis will be performed separately for groups: children born preterm with cognitive deficits, children born preterm without cognitive deficits, and children born at-term with normal cognitive function.

In the first step, we will calculate correlation coefficients between each pair of regions within the specified volumes for each group. These correlations will be adjusted for potential confounding variables, including age, sex, socioeconomic status (SES). To control for multiple comparisons, FDR correction will be applied when assessing significant structural covariance between each pair of cortical regions.

In the second step, Fisher’s r-to-z transformation will be applied to the significant structural covariance connections to standardize the correlation coefficients.

Finally, we will assess between-group differences in cognitive structural covariance networks using a z-test. Specifically, we will compare the networks of preterm children with cognitive deficits against those of preterm children without cognitive deficits, and against those of term-born children with normal cognitive function.

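### The subcortical volume regressions include no measure of head size, so the plan cannot tell a smaller head from a reduction specific to subcortical structures

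*SAP*

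**What the plan says.** The Outcomes section states: "Cortical thickness from DK atlas and subcortical volumes will be used". The Hypotheses section predicts, for preterm children with deficits, "smaller subcortical volumes at 10 years of age compared to both children born before 34 weeks without cognitive deficits" and also compared with term-born children without deficits. It names no structure and does not say whether volume is meant in absolute terms or relative to head size.

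The Analysis section gives the model: "Linear regression model will be used to investigate whether brain structures (cortical thickness and subcortical volumes) differ between children with and without cognitive deficits". The Covariates section lists "Age at time of MR scan, Sex, Socio-economic status (maternal education, household income, and neighbor area index), and scanner sites" and gives the reason: "These variables were selected as they known to be associated with cognitive outcomes or brain development". The Secondary analysis section closes the matter for the regressions: "All models will be adjusted for above-mentioned confounders/covariates".

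For the structural covariance networks (SCN), "we will calculate correlation coefficients between each pair of regions within the specified volumes for each group", and then "These correlations will be adjusted for potential confounding variables, including age, sex, socioeconomic status (SES"). The three sensitivity analyses concern neonatal complications, poor intrauterine growth and an interaction with SES. Intracranial volume, total brain volume, head size and proportional volume are not mentioned anywhere in the SAP.

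**The concern.** The absolute volume of a subcortical structure generally rises with head size. If children with deficits have smaller heads than their comparators after the listed covariates are taken into account, each structure that scales with head size will tend to look smaller, even where no structure is reduced beyond what its head size implies. One global difference would then be reported as a series of structural ones, all in the predicted direction.

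Age, sex, SES and site can absorb part of the variation in head size, but nothing in the plan ensures that they absorb all of it. Head size also plausibly meets the SAP's own criterion for a covariate, an association with cognition or brain development, yet it is left out without comment. What is at stake is the interpretation: whether a finding can be described as specific to subcortical structures or only as lower volume overall.

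**Working it through.** **No figure to reproduce.** The SAP states no group sizes, power, effect size or head-size data; it gives only the whole-cohort size of 11,875. All numerical inputs below are assumptions.

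**Step 1: is head size handled anywhere?**
- Regression covariates (Covariates, applied by Secondary analysis): age at scan, sex, three SES components, scanner site. No head-size measure.
- SCN adjustment: age, sex, SES. No head-size measure is named, although the list is introduced with a word that leaves it open.
- Sensitivity analyses: none on head size.

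**Step 2: apparent difference from head size alone.** Suppose that, after the listed covariates, volume = ρ × ICV + noise in within-group SD units, and that group has no effect on volume except through ICV. With a residual group difference in ICV of δ, the regression without ICV estimates a difference of ρ × δ. The assumed ranges are δ = 0.2 to 0.4 SD and ρ = 0.5 to 0.7. Both must be read as residual values; raw values would probably overstate the effect.

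| | δ = 0.2 | δ = 0.4 |
|---|---|---|
| ρ = 0.5 | 0.5 × 0.2 = 0.10 | 0.5 × 0.4 = 0.20 |
| ρ = 0.7 | 0.7 × 0.2 = 0.14 | 0.7 × 0.4 = 0.28 |

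**Step 3: how often would this be called significant?** Take one case inside that range: δ = 0.3, ρ = 0.6, and 200 children per group (also assumed).
- Apparent difference: 0.6 × 0.3 = 0.18 SD.
- Noncentrality: 0.18 / √(1/200 + 1/200) = 0.18 / 0.10 = 1.8, which gives about 44% rejection per structure at two-sided 0.05.
- Simulation with 14 structures and 1,000 runs, without ICV: mean difference -0.18, rejection 43.7% per structure, all 14 estimates negative in 71% of runs.
- Same data with ICV in the model: mean difference 0.00, rejection 4.9%.
- With 100 per group, rejection without ICV falls to about 25%, and all 14 estimates are negative in about 46% of runs.

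The shift is therefore common to all structures in expectation, but significance depends heavily on group sizes that the SAP does not give.

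**Step 4: SCN.** Under the same model, two volumes related only through ICV have correlation ρ², that is 0.5² = 0.25 to 0.7² = 0.49. This is a correlation within a group. It can affect which edges pass the first-step FDR screen. The hypothesis, however, is tested by a z-test between groups. If ρ and the spread of ICV are the same in both groups, the induced part is the same on both sides and cancels in expectation. A bias in the contrast needs a difference in spread or loading between groups, and the document gives nothing from which to size one. It is also unclear how many edges involve volumes: the correlation step refers to volumes, whereas the FDR step refers to cortical pairs.

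**The case against.** The strongest reply is that absolute volume may be exactly what the SAP intends. The mixed regional pattern in the Hypotheses section concerns cortical thickness, and the network pattern concerns structural covariance. For the subcortex the text predicts only smaller volumes, and a global reduction would fit that wording. Reduced head growth may also lie on the pathway from preterm birth, or from the cause of the deficit, to smaller structures, so that conditioning on ICV would remove part of the effect of interest. This stands. It is why the ICV-adjusted model should sit beside the planned one and not automatically replace it. The argument about preterm birth as the cause is weaker for the primary contrasts, which compare children with and without deficits within a gestational stratum, but it is not removed. The SAP does not state the choice either way.

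It also stands that a residual head-size difference in this sample is plausible but not documented, and that the illustration depends on assumed inputs.

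A reader might infer three stronger things that the SAP does not support:
- That every structure will show a significant deficit. The shift holds in expectation for structures that scale with head size; in the worked case fewer than half of the tests reach significance.
- That the SCN group comparisons are biased by correlations of 0.25 to 0.49. Those figures describe correlations within groups, largely cancel in the contrast if the groups are alike, and the SCN covariate list is not strictly closed.
- That the planned volume model is invalid, or that absolute volume must become secondary. Which of the two is the main estimand is the sponsor's choice.

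Nothing here extends to the cortical thickness regressions.

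**Conclusion.** The point holds for the subcortical volume regressions. As written, they cannot distinguish a smaller head from a reduction specific to subcortical structures, and no sensitivity analysis fills the gap. The illustrative size is 0.10 to 0.28 SD per structure with no regional effect, conditional on the assumed residual ICV difference and correlation; the true size cannot be derived from the SAP. For the SCN the point is narrower: shared head size can influence the edge screen, and it can bias the group contrast only if its spread or loadings differ between groups, by an amount that cannot be estimated here. This is an inexpensive improvement to what can be concluded, not a fault that invalidates the planned analysis.

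**What to change.** In the Covariates and Analysis sections:
1. Pre-specify each subcortical volume regression twice, with and without FreeSurfer intracranial volume as a covariate, and report both.
2. State which is the main estimand, absolute or relative volume.
3. State that a structure-specific reduction will be claimed only if it holds in the ICV-adjusted model.

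In the SCN section, add ICV to the partial-correlation covariates for any edge that involves a volume. Leave the cortical thickness regressions unchanged.

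The cost is some SAP wording and one extra model per structure. Intracranial volume is a standard output of FreeSurfer, with which the Brain outcomes section says the images have already been processed. The downside is that the ICV-adjusted estimate describes relative volume and may remove part of an effect acting through head growth, which is the reason for reporting both. The choice should be fixed now, because the SAP is registered before the data are analysed.

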**Statistics**

Maternal and child characteristics will be summarized using means and standard deviations for continuous variables and frequencies with counts for categorical distributions.

To compare demographic and clinical characteristics between children born very preterm, born moderately preterm and born at term, independent samples t-test and χ^2^/Fisher exact tests will be employed.

**Analysis**

Linear regression model will be used to investigate whether brain structures (cortical thickness and subcortical volumes) differ between children with and without cognitive deficits (presented as standardized beta and 95% CI)

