**Sample size**

This longitudinal cohort consists of 11,875 children, enrolled at baseline (9-10 years) and followed up annually at 21 research sites across the United States. Children were excluded if they were born extremely preterm (< 28 weeks), had a birth weight below 1200g, were not proficient in English, had neurological problems, a history of seizures, or a contraindication for undergoing brain magnetic resonance imaging (MRI) scans.

Since ABCD cohort includes twins and siblings, we will randomly select one child per family to eliminate this source of bias.

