**Primary analysis:**

- Very preterm with cognitive deficits Vs. Very preterm without cognitive deficits
- Moderately preterm with cognitive deficits Vs. Moderately preterm without cognitive deficits

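### The default regression interval in the secondary contrasts takes its residual variance almost entirely from the full-term children, so its coverage depends on an equal-variance assumption that the SAP neither states nor supports

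*SAP*

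**What the plan says.** The whole model specification is one sentence under Analysis: "Linear regression model will be used to investigate whether brain structures", meaning cortical thickness and subcortical volumes, differ by cognitive-deficit status, with results "presented as standardized beta and 95% CI". No variance assumption and no type of standard error is named there or elsewhere.

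The primary contrasts stay within a gestational stratum, for example "Very preterm with cognitive deficits Vs. Very preterm without cognitive deficits", with the same comparison in the moderately preterm. Only the secondary contrasts bring in term-born children: "Very preterm with cognitive deficits Vs. full-term without cognitive deficits" and "Moderately preterm with cognitive deficits Vs. full-term without cognitive deficits". All models are adjusted for age at scan, sex, three socio-economic measures and scanner site.

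The only relevant count is the cohort total: "This longitudinal cohort consists of 11,875 children, enrolled at baseline (9-10 years". No analysis group has a stated size or SD.

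**The concern.** A linear-regression interval with no further qualification is, in practice, the common-variance interval. With balanced groups, unequal variances do little harm to it. With one group far smaller than the other, the estimated residual variance is essentially that of the large group, whereas the sampling error of the difference is essentially the small group's variance divided by its own n.

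The secondary contrasts have this shape by design. The deficit groups are slices (1–2 SD below the control mean on the cognitive composite) of two preterm strata already reduced by the exclusions below 28 weeks and below 1200 g. The full-term group is 39–40 weeks, without deficits, from a cohort of 11,875.

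If the deficit group is more variable than the full-term group, the intervals are too narrow and false differences become more frequent. If it is less variable, the intervals are too wide and power is lost. Recruiting more full-term children does not help, because the error depends on the ratio of the SDs.

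**Working it through.** The SAP has no sample size, power or SD figure to reproduce, so the check asks how far a nominal 95% interval can be off.

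**Inputs.** From the SAP: the model and 95% level (Analysis); the contrasts (Primary and Secondary analysis); the deficit band (Cognitive outcomes); the cohort total and 21 sites (Sample size). Assumed, because the SAP gives no values: n₁ = 15–100 children with deficits, n₂ = 3,000–5,000 full-term children, and r = residual SD of the deficit group divided by that of the comparator, from 0.8 to 1.5. For scale, a band 1–2 SD below the mean holds 13.6% of a normal distribution, or 20–24% if the preterm mean lies 0.3–0.5 SD lower (also an assumption).

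**Step 1: where the variance estimate comes from.** The deficit group's weight in the pooled variance is (n₁ − 1)/(n₁ + n₂ − 2).
- 15 vs 5,000: 14/5,013 = 0.3%
- 60 vs 3,000: 59/3,058 = 1.9%
- 100 vs 3,000: 99/3,098 = 3.2%

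The full-term children therefore carry about 97% or more of the weight.

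**Step 2: where the true uncertainty comes from.** The true variance of the difference, in units of the comparator variance, is r²/n₁ + 1/n₂. At r = 1 the deficit group's share is n₂/(n₁ + n₂): 3,000/3,100 = 96.8% for 100 vs 3,000, and 5,000/5,015 = 99.7% for 15 vs 5,000.

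**Step 3: resulting error rate.** Type I error = 2[1 − Φ(1.96 × SE_pooled/SE_true)], with SE_pooled² = s_p²(1/n₁ + 1/n₂), s_p² = [(n₁ − 1)r² + (n₂ − 1)]/(n₁ + n₂ − 2) and SE_true² = r²/n₁ + 1/n₂.

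Example, 30 vs 4,000 at r = 1.5: s_p² = (29 × 2.25 + 3,999)/4,028 = 1.009; SE_pooled = 0.184; SE_true = 0.274; type I error = 2[1 − Φ(1.315)] = 0.188. When n₁ is far below n₂ the formula reduces to 2[1 − Φ(1.96/r)].

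| r | Secondary contrasts: type I error | Coverage of nominal 95% CI |
|---|---|---|
| 0.8 | about 0.015 | about 98.5% |
| 0.9 | about 0.03 | about 97% |
| 1.0 | 0.05 | 95% |
| 1.1 | about 0.075 | about 92.5% |
| 1.2 | about 0.10 | about 90% |
| 1.5 | 0.18–0.19 | 81–82% |

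**Step 4: do the planned covariates change this?** No. Simulations with 21 site indicators and five covariates, for 20–100 vs 4,000, gave type I error for ordinary regression of 0.015–0.016 at r = 0.8, 0.09–0.10 at 1.2 and 0.18–0.19 at 1.5. Heteroscedasticity-consistent standard errors gave 0.046–0.062.

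**Step 5: primary contrasts.** For assumed sizes from 15 vs 85 to 60 vs 240, the deficit group's weight is 14–20%. Without covariates, coverage is 97.5–97.8% at r = 0.8, 93.3–93.6% at 1.1 and 86.2–87.8% at 1.5. With covariates, type I error was 0.08 at 1.2 and 0.11 at 1.5.

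**Step 6: do the alternatives work?** Without covariates, for 15–60 vs 4,000 and r from 0.8 to 1.5, Welch intervals cover 94.6–95.3%. HC3 with ordinary residual degrees of freedom covers 93.6–94.9%, and is lowest at n₁ = 15. With covariates in the small primary contrast (25 vs 120, equal variances), HC3 gave type I error of 0.031 against 0.049 for ordinary regression; at 60 vs 240 it gave 0.038. Plain HC3 is therefore slightly liberal at the smallest secondary sizes and conservative in the small adjusted primary contrasts.

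**The case against.** The strongest reply is that the SAP never writes down an equal-variance assumption. It leaves the standard error unnamed, and a request for robust errors could be made of almost any unbalanced regression. The first part is correct: common variance is the default reading, not a quotation. The reply does not remove the point. In a plan registered before analysis, silence means either the default interval or a later choice, and the imbalance in the secondary contrasts makes this default unusually sensitive.

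Three stronger readings are tempting, and the SAP does not support them.

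- **That all the regressions have this problem to the same degree.** The primary contrasts contain no full-term children. If all groups were fitted in one model, the full-term variance would dominate there too, but the SAP does not say that this is planned.
- **That the SAP itself predicts unequal variances, because it expects structural covariance to differ** ("We expect higher structural covariance (stronger connection/coordination) in primary sensory networks"). Its covariance analysis uses partial correlations and Fisher's transformation. Correlations are scale-free and can differ between groups while every regional SD is equal.
- **That the intervals are known to be wrong, or too narrow.** Neonatal complications and poor intrauterine growth, which the SAP takes up in sensitivity analyses, could widen spread in the preterm group. Restricting the deficit group to a 1 SD cognitive band could narrow it. The direction is open, and a 10% SD difference moves the error rate only to about 0.03 or 0.075.

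**Conclusion.** The point holds for the two secondary contrasts, as a conditional weakness. If residual SDs are equal, nothing is lost. If they differ by 20–50% with the deficit group more variable, type I error is roughly two to four times nominal (0.09–0.10 to 0.18–0.19). If the deficit group's SD is 20% smaller, the test is conservative at about 0.015. These figures rest on assumed group sizes and SD ratios and on reading the regression as ordinary least squares fitted to the two groups in each contrast. Within 15–100 vs 3,000–5,000 the results hardly depend on the exact sizes. The primary contrasts share the weakness in milder form. This is worth changing before analysis because the remedy is cheap and does not require knowing which way the variances differ.

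**What to change.** Under Analysis, add that the secondary contrasts will use a linear model with group-specific residual variances, or heteroscedasticity-consistent standard errors with small-sample (Satterthwaite-type) degrees of freedom, and that n and residual SD will be reported for each group. State also whether each contrast is fitted on its own two groups or all groups enter one model.

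For the primary contrasts, use the same small-sample-corrected approach (for example HC2 with Satterthwaite-type degrees of freedom) as a check beside the default interval. Plain HC3 is not recommended there, because it was conservative at small n with site indicators. In a two-group comparison without covariates, HC2 with Satterthwaite degrees of freedom is the Welch interval checked above; the covariate-adjusted version was not simulated here.

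The cost is a sentence or two in the SAP and a standard error that may take more than a default software option. The intervals will be slightly wider if the variances are in fact equal.

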**Cognitive outcomes**

The neurocognitive battery, designed for completion in 70 minutes, began with Snellen vision chart to assess visual acuity, excluding children with legal blindness. The battery includes ten measures, seven from NIH Toolbox: Picture Vocabulary, Oral Reading Recognition, Pattern Comparison, Processing Speed, List-Sorting Working Memory, Picture Sequence Memory, Flanker, and Dimensional Change Card Sort. The ABCD study team also assessed Little Man Task (LMT) and Rey Auditory Verbal Learning Test (RAVLT). All tests were administered on an iPad with one-on-one monitoring by a research-assistant.

Cognitive deficit will be defined as a score between 1-2 standard deviation below the control group mean, based on the fully age-corrected composite score from the NIH Toolbox.

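### The SAP reports its four two-group contrasts only as an undefined standardized beta; under the usual meaning its size depends on group shares, so results against preterm and full-term comparators are not on one scale

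*SAP*

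**What the plan says.** The regression outcomes are continuous: the thickness of cortical regions and the volumes of subcortical ones. The Analysis section asks, by linear regression, whether these "differ between children with and without cognitive deficits (presented as standardized beta and 95% CI". The SAP does not say whether the group variable, the outcome or both are standardized. It mentions no mean difference, Cohen's d or raw-unit estimate.

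Every regression contrast has a two-level predictor. The Primary analysis section sets deficit against no deficit within each preterm group, for example "Very preterm with cognitive deficits Vs. Very preterm without cognitive deficits". The Secondary analysis section keeps the same deficit groups and changes the comparator, for example "Very preterm with cognitive deficits Vs. full-term without cognitive deficits". All models are adjusted for the listed covariates.

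The Hypotheses section expects the deficit group to differ when "compared to both children born before 34 weeks without cognitive deficits and those born at term without cognitive deficits", so both sets of results bear on the same hypothesis.

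On numbers, the Sample size section says only "This longitudinal cohort consists of 11,875 children", before exclusions and before "we will randomly select one child per family to eliminate this source of bias". No count is given for very preterm, moderately preterm or full-term children, or for children with a deficit.

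**The concern.** In ordinary usage a standardized beta is the raw coefficient multiplied by SD(predictor)/SD(outcome). That is sensible for a continuous predictor. For a yes/no group variable, SD(predictor) is set by how many children fall on each side. It reflects recruitment and the deficit cut-off, not brain structure.

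The two sets of contrasts are likely to differ sharply in this respect. In the primary contrasts the deficit group is a moderate fraction of a preterm stratum. In the secondary contrasts the same children are probably set against a much larger full-term group, so their share may fall to a few percent or less. If the brain differences were equal, the full-term beta would be smaller from scaling alone. Because the hypothesis names both comparators, a reader will naturally set the two betas side by side. That reader could conclude that the pattern is strong among preterm children and weak against term-born children when the data show no such thing.

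**Working it through.** The SAP states no effect size or group size, so there is no figure of its own to reproduce. The check uses the definition of the measure and assumed sizes.

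**Formula (unadjusted).** With group coded 0/1, p the deficit group's share of the contrast sample, and a difference of d within-group SDs:

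- SD(x) = √(p(1−p))
- SD(y) = √(1 + d²p(1−p))
- both scaled: beta = d·SD(x)/SD(y)
- outcome only scaled: d/SD(y)

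**Worked example, d = 0.40 (assumed).**

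- 40 vs 160: p = 0.20, SD(x) = 0.400, beta = 0.160/1.013 = 0.158.
- 40 vs 3,000 full-term children without deficit: p = 40/3,040 = 0.0132, SD(x) = 0.114, beta = 0.0456/1.001 = 0.046.

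A simulation of 2,000 replicates with a true difference of −0.40 SD gave:

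| Measure | 40 vs 160 | 40 vs 3,000 |
|---|---|---|
| Both scaled | −0.156 | −0.045 |
| Outcome only scaled | −0.390 | −0.397 |

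The first row differs by a factor of about 3.4. The second is nearly constant.

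**Range over assumed sizes, d = 0.40.** The SAP's deficit definition ("Cognitive deficit will be defined as a score between 1-2 standard deviation below the control group mean") covers 13.6% of a normal distribution centred on the control mean. If the preterm mean is 0.2–0.5 SD lower (assumed), it covers 17.6–24.2%. The range 13.6–30% was used. Full-term totals are multiplied by 0.84, the normal-theory share lying no more than 1 SD below the mean. The preterm comparator is all remaining children in the stratum.

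| Preterm children in stratum | Deficit share | Full-term total | Beta, preterm comparator | Beta, full-term comparator | Ratio |
|---|---|---|---|---|---|
| 500 | 30% | 1,000 | 0.180 | 0.142 | 1.3 |
| 300 | 20% | 1,000 | 0.158 | 0.099 | 1.6 |
| 200 | 20% | 3,000 | 0.158 | 0.050 | 3.2 |
| 100 | 20% | 6,000 | 0.158 | 0.025 | 6.3 |
| 50 | 13.6% | 7,000 | 0.136 | 0.014 | 10.0 |

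The 200/3,000 row differs slightly from the worked example because here 3,000 × 0.84 = 2,520 children form the comparator. The last row has only about 7 deficit children (50 × 0.136 = 6.8), so it marks an extreme.

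**Within the primary contrasts.** Moving the deficit share from 20% to 40% moves beta only from 0.16 to 0.19 at d = 0.40. The very preterm and moderately preterm betas are therefore little distorted relative to each other.

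**Adjustment.** These figures are unadjusted. Covariates change the coefficient and its precision, but a fully standardized coefficient still carries the factor √(p(1−p)).

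**The case against.** The strongest reply is that the SAP never says the group variable is scaled. A coefficient on a 0/1 group with a z-scored outcome is also reported under this name, and then almost nothing is wrong. This stands. The point is conditional on the usual meaning; otherwise the fault is only that the measure is undefined.

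Second, with no group sizes in the SAP, no particular multiple is a property of the plan. This also stands, so every multiple above is an assumption.

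Third, nothing inferential moves. Rescaling leaves the t-statistic and p-value unchanged. The hypotheses predict directions against each comparator and do not rank the two contrasts. Networks are carried forward on significance, not on the size of a beta. All of this is correct, and it limits the point to how effect sizes and intervals are read.

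Fourth, the SAP lists contrasts and refers to models without saying that each is fitted in its own two-group subset. In one joint model the outcome SD would be common to the contrasts. Any scaled group indicator would still carry its group's share.

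A reader might go further and infer that the reported effects and intervals will be wrong, or that the full-term contrasts will certainly be understated several-fold. The document supports neither, because it fixes neither the standardization nor the group sizes.

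**Conclusion.** The point holds as a cheap improvement to the effect measure, not as a proven error. If predictor and outcome are both scaled and each contrast is fitted in its own two groups, the same brain difference appears smaller against a larger full-term comparator, by about 1.3- to 10-fold over the assumed sizes. What is at risk is the magnitude of the reported effects and their confidence intervals, and the comparison of that magnitude across the two comparators in the hypothesis. Tests, p-values and network selection are not at risk, and the distortion between the two primary contrasts is small.

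**What to change.** In the Analysis section, replace the standardized beta with the covariate-adjusted mean difference between groups and its 95% CI. Keep the group coded 0/1. Divide each outcome by one fixed SD used in all four contrasts, for example that region's SD in the full-term group; another common SD is also acceptable if it is named in advance. Give the raw difference alongside, in mm for thickness and mm³ for volume.

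This costs one sentence in the SAP and a line of code, with no extra data and no change to any test. The SAP is registered before the data are analysed, so the measure can be fixed now. The downside is that the values will not match fully standardized betas in other reports.
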